### General statistical analysis plan

#### a) Primary outcome measure

The proportion of women who report prolonged and total abstinence from smoking immediately before child birth will be compared between treatment groups by Chi-squared test, on an intention to treat basis (all those randomised) with smokers lost to follow up considered to have continued smoking. For this analysis, we will assume that women in each group use their allocated treatments as directed and no randomised participants will be excluded from analyses. Baseline data on smoking behaviour and demographic information will be compared between groups, and adjustment made for any differences, using logistic regression.

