### Randomised procedure

After collecting pre-randomisation baseline data, exhaled carbon monoxide readings will be taken from women and assuming that readings indicate that women do smoke [cut off 8 ppm [17]], informed consent for trial entry will be sought. After consenting to trial entry, women will receive an initial behavioural support session before being randomised. Full details are given later.

Randomisation will be via the Nottingham Trials Unit web-based database and randomisation service. In each centre the recruiting research midwife (RM) will have a username and password. (S)he will log on to the trial website that hosts the trial database, confirm that the patient eligibility criteria are all met and enter an agreed minimum amount of *registration *data about the participant and centre before randomisation is possible. Data to be entered at this stage are described later. The computer will then issue a trial number which will be the unique identifier for the trial participant and a trial pack number which will reflect the treatment allocated. Randomisation will be stratified by trial centre only.

Numbered packs of active and placebo patches will be distributed by Queens Medical Centre pharmacy and stored in all participating ante-natal/ultrasound clinics. After randomisation, the research midwife will select the patch pack with the appropriate number and issue this to the participant. The research midwife and the trial participant will both be blind to group allocation. The research midwife will issue NRT/placebo under the supervision of a senior, local doctor via a patient group directive (PGD) [18]. When research midwives visit women at home to enrol them into the trial, immediate internet randomisation will not be possible. In this circumstance the research midwife will return to her/his hospital base to randomise the enrolled woman and the appropriate trial pack will be posted to the trial participant.

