##### i) Mandatory enrolment data (i.e. required for randomisation)

The RM will collect the following data from participants immediately after obtaining informed consent. The RM **must **enter the following data items about participants to the online database **before **randomisation is permitted:

*DoB *(valid range equiv to age 14–50)

participant's initials

hospital number

*daily number of cigarettes smoked before pregnancy*[28]

*daily number of cigarettes smoked currently*[28]

*agreed gestational age at time of randomisation *(valid range 12^0^–24^6^) [estimated delivery date will be calculated automatically within database]

time elapsed since last cigarette

exhaled CO reading of at last 8 ppm

*blood sample requested *(for cotinine assay, DNA extraction & storage)

indication that patient has signed consent form

*indication that participant's contact details have been recorded on paper *(see below)

agreed quit date

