##### ii) Remaining baseline data for online entry

The following data will be collected with above data and the RM will also enter this on to the online database but entering these variables will **not **be mandatory before online randomisation is permitted.

*NHS number *(for ONS registration)

ethnic group

age left full time education

*number of previous births beyond 24 weeks *(valid range 0–12)

*time to first cigarette of day *[29]

partner's smoking status

maternal height

maternal weight at booking appointment

saliva sample

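### The adjusted analysis of the primary outcome takes its covariates from observed baseline differences between arms, so its model is fixed by chance imbalance after the data are seen

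*Protocol article*

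**What the plan says.** In the protocol article, General statistical analysis plan, a) Primary outcome measure, the proportion with prolonged abstinence "will be compared between treatment groups by Chi-squared test, on an intention to treat basis (all those randomised"), with women lost to follow-up counted as smokers. The paragraph then adds a second analysis: "Baseline data on smoking behaviour and demographic information will be compared between groups, and adjustment made for any differences, using logistic regression". No variable is named for this model, what counts as a difference is not defined, and the two analyses are not ranked.

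Four other places bear on the point:

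- Randomised procedure: "Randomisation will be stratified by trial centre only".
- Data collection, a) Baseline: entry of "daily number of cigarettes smoked currently" is required before randomisation. Entry of "time to first cigarette of day", "partner's smoking status" and age at leaving full-time education is not.
- d) Sub group analyses: baseline cotinine and maternal education enter logistic models of cessation with treatment group, but to study effect modification.
- Sample size: the calculation compares two cessation rates, 16% and 25%, and uses no covariates.

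**The concern.** In a properly randomised trial a baseline difference between arms is chance. A rule that adjusts for whatever differs therefore picks covariates by luck and not by how well they predict quitting. A strong predictor that happens to balance stays out, and a weak one that happens to differ goes in. Centre, which the allocation is stratified on, is neither smoking behaviour nor demography and is balanced by design, so the rule cannot be relied on to include it.

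Because a difference is not defined, two analysts could follow the sentence faithfully and fit different models, each chosen with the data in view. If the chi-squared test and the adjusted model fell on opposite sides of 5%, nothing in the text would settle which one stands.

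This is more than detail left to an analysis plan that is not shown. The protocol states the selection rule, and a later plan that named its covariates in advance would depart from it.

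**Working it through.** **1. The plan's own power figure.** Inputs from Sample size: 500 per arm, p1 = 0.16, p2 = 0.25, two-sided 5%.

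- Mean rate 0.205. Null SE = √(2 × 0.205 × 0.795 / 500) = 0.02553.
- Alternative SE = √((0.16 × 0.84 + 0.25 × 0.75) / 500) = 0.02537.
- Power = Φ((0.09 − 1.96 × 0.02553) / 0.02537) = Φ(1.57) = 94.2%. With continuity correction (subtract 1/500 from the difference) it is Φ(1.50) = 93.3%. The protocol states 93%.
- The second stated figure, 80% for a 7-point difference, comes out at 79.9%.

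The stated power reproduces as an unadjusted comparison of two proportions, so the covariate rule does not enter the sample size.

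**2. How often the rule selects anything.** Assume that a difference means p<0.05 and that k independent variables are compared. The chance that at least one is flagged by randomisation alone is 1 − 0.95^k:

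| k | At least one flagged | None flagged |
|---|---|---|
| 5 | 22.6% | 77.4% |
| 6 | 26.5% | 73.5% |
| 8 | 33.7% | 66.3% |
| 10 | 40.1% | 59.9% |

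Independence matters. With six variables at pairwise correlation 0.5 (also assumed), simulation gave 21%.

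**3. What the rule costs.** Trials of 525 per arm were simulated at 16% v 25% and under the null, with independent normal covariates and p<0.05 as the trigger. Covariate strengths are assumptions, and centre was not simulated.

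- Setting A: eight covariates, three prognostic at log OR 0.5 per SD; unadjusted logistic test in place of chi-squared; 6,000 null and 4,000 alternative trials.
- Setting B: six covariates with log ORs 0.35, 0.35, 0.25, 0, 0, 0 per SD; run twice, both results shown.

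| | Unadjusted | Chosen by imbalance | Prespecified |
|---|---|---|---|
| Power, A | 94.7% | 95.0% | 96.4% |
| Power, B | 95.1%, 95.2% | 95.3%, 95.4% | 96.1%, 96.1% |
| Type I error, A | 5.4% | 5.1% | 5.3% |
| Type I error, B | 5.0%, 5.2% | 4.8%, 4.9% | 4.9%, 5.0% |

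Power forgone by the rule against the prespecified model is 96.4 − 95.0 = 1.4 points in A, and 96.1 − 95.3 = 0.8 and 96.1 − 95.4 = 0.7 in B. Taking the better of the chi-squared and imbalance-chosen results in B gave 5.1% type I error against 5.0% for chi-squared alone (10,000 null trials). The Monte Carlo standard error in A is √(0.05 × 0.95 / 6,000) = 0.3 points, so none of these runs shows inflation.

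**4. What the adjusted odds ratio estimates.** In A the mean log ORs were 0.558 (unadjusted), 0.561 (chosen by imbalance) and 0.625 (prespecified), that is odds ratios of e^0.558 = 1.75, e^0.561 = 1.75 and e^0.625 = 1.87. This gap is not bias. An odds ratio conditional on predictors is further from 1 than the marginal one. The SD of the estimate also rises, from 0.159 to 0.169. The gain from prespecified adjustment is in the ratio: 0.558 / 0.159 = 3.5 against 0.625 / 0.169 = 3.7. So under the rule the quantity being estimated depends on which variables chance flags, and on average it stays close to the unadjusted one.

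**The case against.** The strongest reply is that the primary test is not in doubt. The chi-squared test comes first under the primary outcome heading, covers all randomised women, needs no baseline data and matches the basis of the sample size. On the natural reading the logistic model is a supporting analysis. That stands. A reader might infer two co-equal primary answers, or a primary conclusion that rests on chance imbalance. The text supports neither; what it lacks is a sentence ranking the two.

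The second reply is that the numbers show little harm. That also stands. A reader might infer an inflated error rate or a serious loss of power, and the simulations show neither.

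Third, the 26.5% depends on reading a difference as p<0.05 and on six independent variables. The comparison might be descriptive, and smoking measures plausibly correlate. This is fair, but a descriptive reading leaves the choice of covariates more open, not less.

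Fourth, the protocol does not establish which baseline variables predict quitting, and it already plans logistic models with cotinine and education whatever the balance. Those models serve subgroup questions and do not supply a prespecified adjusted primary estimate. The candidate covariates are a judgement and should be presented as one.

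Last, covariate lists are commonly left to the analysis plan. That would answer a silent protocol. This one states a rule.

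**Conclusion.** The point holds for the adjusted analysis only. The protocol commits to a covariate rule driven by chance imbalance, which can omit centre and strong predictors that balance, and it does not say which result decides if the two differ. The main harm is an adjusted estimate that is not prespecified and is open to choice.

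The size is modest: about 1 point of power at 16% v 25%, from a base near 95%, with type I error essentially unchanged. These figures rest on assumed covariate strengths, independence and a p<0.05 trigger, none of which is in the protocol. The chi-squared test, its error rate and the sample size are unaffected. It is worth correcting because correction is nearly free, not because the primary conclusion is at risk.

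**What to change.** - Remove the baseline comparison as the trigger for adjustment. A descriptive baseline table can stay.
- State that the chi-squared test is decisive and the adjusted model supportive, or name the adjusted model as primary.
- Name the adjusted logistic model now: treatment, centre and a short list of baseline factors already collected. Candidates are current cigarettes per day or baseline cotinine, time to first cigarette of the day, partner's smoking and age at leaving education. Fit it whatever the observed balance.
- Some of these items need not be entered before randomisation, and cotinine depends on a sample being obtained. Specify simple imputation or a missing indicator so that all randomised women stay in the model.

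The cost is two or three sentences in the analysis section, with no new data, visits or participants.

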#### b) Child behaviour and development scores at 2 years

We will compare in children born to women in the control and intervention groups, using t-test (via log transformation) or the Mann-Whitney U statistic. Again this will be done on an intention to treat basis. A small number of children will be born as multiple births (e.g. twins) and data for these cases will be clustered rather than independent. Robust standard errors, or a similar appropriate statistical method will be used in analysis of child data to allow for this.

There will be two analyses. The first will be conducted upon data obtained around delivery. The second will be conducted at 2 years after delivery, using data obtained between delivery and this time point. Data collected for secondary outcomes will not be analysed until the trial has ended with respect to the primary outcome measure.

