### Procedure for administering postal follow up questionnaires

(see Figure 2): After infant deaths, questionnaires will not be sent and, where maternal deaths are reported, infants' general practitioners will be consulted about the appropriateness of continued follow up. The Trial Office will send questionnaires directly to study participants using contact details provided at study recruitment. For non-respondents or where questionnaires are returned labelled "*not at this address*", the office will check participants' addresses by contacting infants' grandparents and, if necessary, the ONS. ONS will trace the infant or mother and provide details of the Primary Care Trust (PCT) which provides their NHS health services and the Trial Office will then contact the infant's general practitioner so that a questionnaire can be sent. To maintain contact between researchers and participants, study infants will be sent Christmas cards and first birthday cards.

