### Follow-up 2 years after childbirth

i) *Parent questionnaire*: Two weeks before infants' 2^nd ^birthdays, we will dispatch to *parents *a questionnaire to measure child behaviour, development, hospital admissions, respiratory symptoms and maternal smoking behaviour. Two weeks later, all participating infants will be sent a 2^nd ^birthday card with a questionnaire reminder for non-respondents. The instrument uses standard questions to record parents' reports of infants' respiratory symptoms [21] and behaviour [22], developed from those used in the MRC-funded UK Oscillation Study [23], with reference to the evidence base for questionnaire design [24].

ii) *Health professional questionnaire*: At the same time as parents' questionnaires are dispatched, we will post participants' general practitioners (GPs) a health professional questionnaire (*HPQ*) to measure children's disability according to a standard definition. [25] This brief instrument is designed to be completed using medical records. Health professionals completing these questionnaires require relatively little knowledge of the patient and GPs will be asked to complete them. If GPs cannot complete HPQs, they will be asked to forward these to children's' health visitors (HV). We will use an initial postal and subsequent telephone reminder to GPs to obtain the required information. The HPQ questionnaire has been validated and used with GPs and HVs previously [26,27] and requests data that HVs collect during their routine clinical practice to provide external validation of parents'.

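### The 2-year child behaviour and development scores are compared by unadjusted two-group tests; one pre-specified regression clustered on the mother would use recorded covariates and centre and give an interval, for a modest gain in precision

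*Protocol article*

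**What the plan says.** Part b) of the general statistical analysis plan, on child behaviour and development scores at 2 years, compares the arms "using t-test (via log transformation) or the Mann-Whitney U statistic", by intention to treat. It names no covariate and gives no rule for choosing between the two tests. It then turns to twins: "A small number of children will be born as multiple births (e.g. twins) and data for these cases will be clustered rather than independent". The remedy is: "Robust standard errors, or a similar appropriate statistical method will be used in analysis of child data to allow for this".

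Covariate adjustment appears in part a), for the primary outcome: "Baseline data on smoking behaviour and demographic information will be compared between groups, and adjustment made for any differences, using logistic regression". That sentence concerns a binary outcome and is triggered by observed imbalance. Nothing carries it over to the child scores.

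The relevant variables are recorded elsewhere in the protocol:

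- Child gender and date of birth are in the data collected around childbirth.
- The mother's "age left full time education" is among the baseline items that are not mandatory before randomisation.
- Centre is the sole stratification factor (Randomised procedure).

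The scores come from "a questionnaire to measure child behaviour, development, hospital admissions, respiratory symptoms and maternal smoking behaviour", posted a fortnight ahead of the second birthday and followed by a reminder. Non-responders are traced through grandparents, the Office for National Statistics and the general practitioner. The 2-year data items do not include a completion date.

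**The concern.** The Background names nicotine as a possible cause of attention and learning problems in childhood, and the trial sets out to judge whether NRT is safe. The 2-year scores bear directly on that question. In a safety comparison, what matters most to the reader is the width of the interval, because an imprecise null result is easily taken as reassurance.

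The named tests fall short in three ways. They use no prognostic information, although sex and maternal education are recorded. They ignore the factor on which randomisation was stratified. And the rank branch, in its plain form, returns a p-value without a mean difference and interval, and treats twins as independent. A single regression model deals with all three.

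**Working it through.** **Does the plan give a figure to reproduce?** Not for these scores: there is no standard deviation, target difference or power. The Sample size section covers smoking cessation only. Its figures do reproduce: 16% against 25% with 500 per arm gives 94.2% power without continuity correction and 93.2% with it (stated 93%), and a 7-point difference gives 79.9% without correction (stated 80%). They say nothing about the child scores, so what follows rests on assumed ranges.

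**Gain from adjustment.** If the covariates explain a share R² of score variance, the standard error is multiplied by √(1 − R²), and the equivalent extra sample is 1/(1 − R²) − 1.

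| Assumed R² | SE multiplier | Fall in SE | Equivalent extra children |
|---|---|---|---|
| 0.05 | 0.975 | 2.5% | 5.3% |
| 0.10 | 0.949 | 5.1% | 11.1% |
| 0.15 | 0.922 | 7.8% | 17.6% |

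**Detectable difference and power.** In standard deviation (SD) units, the difference detectable with 80% power at two-sided 5% is (1.960 + 0.842) × √(2/n) × √(1 − R²). With n = 500 per arm and no adjustment this is 2.802 × 0.0632 = 0.177 SD.

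Power for a difference of 0.20 SD is Φ(0.20 / [√(2/n) × √(1 − R²)] − 1.96). With n = 500 and R² = 0 this is Φ(3.162 − 1.96) = 88.5%. The 500 is the evaluable number in the Sample size section. The 300 is an assumed figure for heavier loss by 2 years. The 0.20 SD is also assumed.

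| R² | Detectable, n = 500 | Power for 0.20 SD, n = 500 | Power for 0.20 SD, n = 300 |
|---|---|---|---|
| 0 | 0.177 SD | 88.5% | 68.8% |
| 0.05 | 0.173 SD | 90.1% | 71.0% |
| 0.10 | 0.168 SD | 91.5% | 73.3% |
| 0.15 | 0.163 SD | 92.9% | 75.7% |

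Over R² of 0.05–0.15 the gain is about 2–4 points of power at 500 per arm and 2–7 points at 300.

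**Effect of twins.** With a share t of pregnancies being twins and within-pair correlation ρ, the design effect is 1 + ρ × 2t/(1 + t). The document says only that multiple births are few, so t = 1–3% and ρ = 0.5–0.9 are assumed.

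- Low end: 1 + 0.5 × 0.02/1.01 = 1.010.
- High end: 1 + 0.9 × 0.06/1.03 = 1.052.

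A nominal 5% test that ignored twins would then have a true error rate of about 5.1–5.6%. A 20,000-run simulation with 400 mothers per arm gave the plain Mann-Whitney test 5.5% at t = 1.5%, ρ = 0.7 and 5.9% at t = 3%, ρ = 0.9, against 5.1% with no twins. Clustering must be handled, but it moves the error rate by less than 1 point from nominal.

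**Do the test and the twin provision fit together?** The t-test on the log scale can be run as a regression of log score on arm with standard errors clustered on the mother, which is the first remedy named. A Mann-Whitney test has no regression standard error to make robust. The provision, however, allows an equivalent method, and a clustered rank-sum test or a mother-level bootstrap would qualify.

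**The case against.** The strongest reply is that the groups are randomised, so an unadjusted comparison is unbiased and keeps its error rate. The whole gain then rests on an R² that the documents do not supply. A general plan in a journal article may also leave covariates for secondary outcomes to the full analysis plan, which is not shown. The first part stands, and it limits the point to precision. The last part stands only in part: the article does not merely leave the method open, it names two tests, and both are unadjusted.

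Four stronger readings are tempting, and the documents do not support them.

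- **That the section contradicts itself**, because a Mann-Whitney test cannot carry robust standard errors. The provision is not limited to robust standard errors, and a clustered rank method satisfies it. This is a loose end.
- **That age at completion is an available covariate that the plan wastes.** Date of birth is recorded, but no completion date is listed for the 2-year questionnaire. Postal follow-up and tracing make some spread in age plausible, but no figure shows how much. Response time also arises after randomisation and could depend on smoking outcome or child health, so it does not belong in the main model.
- **That this is the trial's only look at neurodevelopmental harm.** Disability at 2 years is a separate outcome, measured by a health-professional questionnaire.
- **That the unused covariates are strong predictors.** An assumed joint R² of 5–15% does not justify that word.

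**Conclusion.** The point holds as a modest, nearly free improvement. The planned tests are valid but leave child sex, maternal education and centre unused. The rank branch gives no mean difference with an interval and needs a clustered version to meet the twin provision. The size is a 2.5–8% smaller standard error, equivalent to 5–18% more children, if the covariates explain 5–15% of score variance. That R² is an assumption. Twins add little either way (design effect about 1.01–1.05 under the assumed ranges). Nothing here suggests bias in the planned comparison. Part b) also holds back secondary-outcome data until the trial has ended for the primary outcome, so the wording can be changed before those data are analysed.

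**What to change.** Replace the choice of two tests with one pre-specified main analysis for each score: a linear regression, on a transformed scale if needed, of score on arm, centre, child sex and maternal age at leaving education. Cluster the standard errors on the mother and report the adjusted difference with its 95% confidence interval. Child sex is recorded at birth but fixed before randomisation, so it is safe to include.

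If a score is too skewed for this, use a bootstrap that resamples mothers, or an ordinal model clustered on the mother, with the same covariates. State in advance what triggers that choice. Any rank test becomes a cluster-adjusted sensitivity analysis.

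Record the completion date on each 2-year questionnaire, and use age at completion only in a sensitivity analysis.

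The cost is analysis wording and one extra date field. Education is not mandatory at enrolment, so a simple rule for missing values is also needed, for example filling in the overall mean of the observed values without reference to arm.

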### Sample size

We need to recruit 525 women into each arm of the study. A trial with 500 women in each arm would detect an absolute difference of 9% in smoking cessation rates between the two groups immediately before childbirth with a two-sided significance level of 5% and a power of 93%. We anticipate that up to 5% of women will be lost to follow up and inflate our sample size (of 500) by a factor of 1.05 to allow for this. This size of study would allow us to detect smaller treatment effects with lower power. For example, we would have 80% power to detect an absolute difference in cessation rates of 7%.

A Cochrane review has shown that approximately 10% of women who are still smoking at the time of their first antenatal visit will stop smoking with usual care and a further 6% to 7% will stop as a result of a formal smoking cessation program using intensive behavioural counselling [15]. This means that in our control group (*placebo plus intensive behavioural counselling*) we can expect a smoking cessation rate of around 16%. The most recent Cochrane review of NRT, reports a treatment effect (odds ratio) for transdermal patches of 1.74 95%CI (1.57–1.93) [5]. Consequently, if we were to find NRT as effective in pregnancy as it is generally, we could expect a smoking cessation rate of approximately 25% in our treatment group (*NRT plus intensive behavioural counselling*).

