### Inclusion criteria

Eligible women are women between 12 and 24 weeks pregnant, who report smoking at least ten cigarettes daily *before *pregnancy and who *still currently *smoke at least five cigarettes daily. They also must have an exhaled CO reading at least 8 ppm. Women may only enrol into the trial once and may participate in other non-conflicting research projects.

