#### c) Upon admission for childbirth

The following data are recorded by the RM or delivery suite staff:

Date of follow up/exhaled CO reading or saliva sample

Smoked at all in the 24 hrs prior to delivery

Smoked between quit date and delivery

One or both of, *i) exhaled CO reading & ascertainment date ii) saliva sample *(for cotinine)

On how many days have patches been used?

On how many days (if any) have non-trial patches been used?

How many behavioural support sessions with NHS stop smoking services used (telephone & face to face)?

i) These data obtained by RM from ***maternal ***or ***infant medical records before ***discharge. For reasons of data protection some personal infant details are recorded on paper rather than being transmitted over the internet to the trial database:

*maternal *

hypertension (>140/90) on 2 occasions (excluding labour)

miscarriage (between randomisation and 24 weeks)

labour onset (spontaneous, induced, no labour)

mode of delivery (SVD, instrumental, caesarean)

ante natal or post natal maternal hospital admission

*infant*

baby initials

D.O.B

Gender

Baby NHS number

*Prompt for RM to confirm full name and address and contact details of baby and to record these on paper *(see below)

Prompt for RM to make a new record of contact details if these have differed from previous (i.e. maternal) ones

baby hospital number

birth weight

Number of births

if multiple birth, indicate number and birth order

live or stillbirth?

cord ph < 7.0

Apgar <7 at 5 min

*Gestational age at birth *– to be calculated within database from gestation at recruitment

These infant personal details will be recorded on paper only:

baby name

baby address (inc postcode)

ii) These data obtained by research midwife from ***infant medical records after ***discharge:

If live birth? live on leaving hospital

ventilation > 24 hrs

necrotising enterocolitis

neonatal convulsions

admitted to special care

*intraventricular haemorrhage *(4 categories)

*congenital abnormality present (y/n). If y then free text to describe this*.

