#### c) Other outcomes

i) *Fetal birth outcomes *and ii) *Maternal birth outcomes *will also be compared on an intention to treat basis between the 2 groups in the first analysis at delivery (as *a *&*b *above)

As these outcomes relate to the safety of NRT in pregnancy we will also conduct an analysis of these outcomes comparing participants in each group who report using any patches with those in each group who report using none.

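### Twin births are handled only as a clustering problem in the fetal birth outcomes; adjusting for plurality would recover a modest amount of precision, mainly for gestational age

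*Protocol article*

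**What the plan says.** **Eligibility.** The Inclusion criteria begin "Eligible women are women between 12 and 24 weeks pregnant, who report smoking at least ten cigarettes daily" and set no limit on the number of fetuses. The Exclusion criteria do not mention multiple pregnancy.

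**Handling in the analysis.** Section b) Child behaviour and development scores at 2 years says: "A small number of children will be born as multiple births (e.g. twins) and data for these cases will be clustered rather than independent". It then prescribes robust standard errors, or an equivalent method, for child data. Section c) Other outcomes says that fetal and maternal birth outcomes "will also be compared on an intention to treat basis between the 2 groups in the first analysis at delivery", referring back to the methods of sections a) and b). The same section adds a safety analysis comparing women who used any patches with women who used none.

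**What is compared.** The list under Fetal loss and morbidity includes gestational age at birth and a birth-weight Z score. The Z score is adjusted for gestational age, maternal height, maternal booking weight and ethnic group, but not for the number of fetuses. No adjustment is stated for gestational age.

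**Where plurality appears.** Randomisation is stratified by centre alone. Plurality is in neither list of baseline data. It is first recorded on the delivery form: "if multiple birth, indicate number and birth order".

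**The concern.** Twins raise two separate statistical problems. Siblings' outcomes are correlated, and twins have a different expected outcome from singletons whatever the treatment. Robust standard errors deal with the first. They leave the second in the residual variance, where it widens the interval for the treatment effect.

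Nothing else in the plan picks up the second problem. Stratification is by centre and the Z score omits plurality. The rule in section a) of adjusting for baseline smoking and demographic differences would not reach plurality, because plurality is not among the baseline data.

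What is at stake is the precision and readability of the fetal safety comparison, which is one of the trial's stated aims. The comparison of patch users with non-users is a further matter. It is not randomised, so a difference in plurality between users and non-users would confound it, and robust standard errors do not correct confounding.

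**Working it through.** **The plan's own figure.** The only power statement is for smoking cessation: "A trial with 500 women in each arm would detect an absolute difference of 9% in smoking cessation rates", "with a two-sided significance level of 5% and a power of 93" per cent. For 16% against 25% with 500 per arm:

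- Standard error under no difference: √(2 × 0.205 × 0.795/500) = 0.02553. Under the alternative: √((0.16 × 0.84 + 0.25 × 0.75)/500) = 0.02537.
- Power = Φ((0.09 − 1.96 × 0.02553)/0.02537) = Φ(1.575) = 94.2%. The number needed for 93% power is 473 per arm, or 495 with continuity correction, so the stated figure is reproduced.

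This outcome is counted per woman, so twins do not affect it. The article gives no power, SD or twin rate for birth outcomes.

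**Inputs for the twin question.** From the document: 525 women per arm. Assumed:

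- twin pregnancies t = 1% to 3%;
- Z score: SD σ = 1, twin deficit d = 0.5 to 1.0, within-pair correlation ρ = 0.6;
- gestational age: σ = 2 weeks, d = 2 to 3 weeks, ρ = 1 (twins are born together).

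**Formulae, per arm.** n_t = 525t, n_s = 525(1 − t), N = n_s + 2n_t. Deviations from the pooled mean are r_s = d × 2n_t/N for singletons and r_t = r_s − d for twins.

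- Pooled, cluster-robust: V = [n_s(σ² + r_s²) + n_t(2σ²(1 + ρ) + 4r_t²)]/N²
- Singletons only: V = σ²/n_s
- SE of the arm difference = √(2V)

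**Worked case: gestational age, t = 1.5%, d = 3 weeks.** n_s = 517.125, n_t = 7.875, N = 532.875, r_s = 0.0887, r_t = −2.911.

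- Pooled: (517.125 × 4.0079 + 7.875 × 49.903)/532.875² = 0.008683, so SE = 0.1318 weeks.
- Singletons: 4/517.125 = 0.007735, so SE = 0.1244 weeks. The ratio is 1.059.
- All infants with the singleton–twin difference removed (r terms set to zero, which approximates adjustment): (517.125 × 4 + 7.875 × 16)/532.875² = 0.007728, so SE = 0.1243 weeks. Adjustment recovers essentially all of the loss without dropping anyone.
- The r terms alone, which are the chance-imbalance part, have SD 0.0437 weeks. Since 0.1243² + 0.0437² = 0.1318², the pooled standard error already contains that imbalance.

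**Range** (lowest to highest over the assumed deficits):

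| Twin rate | Gestational age: pooled SE ÷ singleton SE | Z score: pooled SE ÷ singleton SE |
|---|---|---|
| 1% | 1.018–1.041 | 1.001–1.015 |
| 1.5% | 1.027–1.059 | 1.001–1.021 |
| 2% | 1.034–1.076 | 1.001–1.027 |
| 3% | 1.047–1.106 | 1.000–1.037 |

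For an effect that the singleton analysis would detect with 80% power, pooled power is 72% to 79% for gestational age and 77% to 80% for the Z score.

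**Validity.** Simulated type I error of the pooled comparison with cluster-robust standard errors was 4.96% for the Z score, and 4.96% and 5.09% for gestational age at 1.5% and 3% twins.

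**Chance of a visible imbalance.** At 1.5% there are 1050 × 0.015 ≈ 16 twin pairs. The chance that they split 2:1 or worse between the arms is about 21%.

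**Patch users against non-users.** The confounding equals the deficit times the difference in twin-infant share. With a deficit of 2 to 3 weeks, each percentage point of difference in that share shifts mean gestation by 0.02 to 0.03 weeks. The documents do not say whether patch use differs by plurality.

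**The case against.** The strongest objection is that covariates and singleton analyses for secondary outcomes are usually left to the analysis plan, which is not shown, and that this is a condensed article. Pooling is also inferred from the cross-reference in section c) rather than stated, and the wording on robust standard errors allows an equivalent method. This limits the weight of the point but does not remove it. The article raises multiple births itself, describes the problem as clustering alone and chooses a remedy for that alone.

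Several stronger readings are tempting, and the documents do not support them:

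- *Twins bias the safety comparison or invalidate the test.* Plurality is balanced by randomisation up to chance, and the robust standard error includes that chance.
- *A woman with twins counts twice.* The planned clustering correction addresses exactly this.
- *Low birth weight and preterm birth are compared outcomes dominated by twins.* They appear only as categories under Safety reporting, not in the outcome list. Nor would twins dominate. Assume low birth weight in 8% to 12% of singletons and 50% to 60% of twins, with twins 2.0% to 3.9% of infants (1% to 2% of pregnancies). Twins then supply between 0.0198 × 0.5/(0.0198 × 0.5 + 0.9802 × 0.12) = 8% and 0.0392 × 0.6/(0.0392 × 0.6 + 0.9608 × 0.08) = 23% of events.
- *The loss can be sized in grams.* The listed outcome is a Z score that already adjusts for gestation, so its loss is smaller.
- *Singletons should be the main analysis.* That would remove randomised women from a comparison specified as intention to treat.

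One further objection stands and shapes the fix. The delivery form records plurality after randomisation, and the number born could change if one twin is lost. The DMEC may already analyse birth outcomes as it sees fit, so a split by plurality helps it rather than filling a gap in its powers.

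**Conclusion.** The point holds as a modest improvement in efficiency. The stated method is valid for the randomised comparison but leaves avoidable variance: about 2% to 11% of the standard error for gestational age and 0% to 4% for the birth-weight Z score. The upper ends need both a 3% twin rate and the larger deficits. At a 1.5% twin rate the figures are about 3% to 6% and 0% to 2%. All of them rest on assumed twin rates, deficits, SDs and correlations.

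The comparison of patch users with non-users is the one place where bias is possible, and only if patch use differs by plurality, on which the documents are silent. The primary outcome, its sample size and its power are unaffected.

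**What to change.** In section c) Other outcomes, state that gestational age at birth and birth-weight Z score are compared in all infants by intention to treat, using a regression model with standard errors clustered on the mother and adjustment for plurality (singleton or multiple). Apply the same adjustment to the comparison of patch users with non-users. Prespecify a singleton-only analysis alongside, so that the choice of infants is made before results are known.

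Take plurality from the antenatal scan where possible, so that it is a pre-randomisation value, and use the delivery form otherwise. Tabulate multiple births by arm, and split the DMEC's birth-weight tables by plurality.

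The cost is a little more analysis work. Plurality at birth is already collected. The scan value is on neither baseline list, so it would be read from the maternal records that the research midwife already consults. Recruitment, eligibility and sample size do not change.
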